### Physical activity levels and sedentary behaviour

Habitual physical activity and time spent in sedentary behaviour will be evaluated at baseline and after 24 weeks of intervention as behavioural parameters, based on accelerometry, using devices of the GT3X and GT3X+ models (Actigraph Pensacola, FL, USA) and Actilife software (Actigraph Pensacola, FL, USA). Each participant will be instructed to use the accelerometer for seven consecutive days, removing it only to sleep, shower or perform water activities. The device will be placed on an elastic belt and fixed on the right side of the hip. Data will be collected at a frequency of 30 Hz and analysed in 60-s epochs. Periods with consecutive zeros for 60 min or more (with a 2 min tolerance) will be interpreted as non-use time and excluded from the analysis. For analysis purposes, a minimum of 10 h of daily activity recordings, for at least 4 days, three weekdays and one weekend day will be considered valid data. The average time spent in each intensity of physical activity and in sedentary behaviour will be calculated from the cut-off points proposed by Freedson et al. [46] and Sasaki et al. [47]. Data will be analysed in minute/day, adjusted for number of days of use and daily time of use. From this, the following outcomes will be analysed: time in sedentary behaviour (minute/day), in light physical activity (minute/day), moderate (minute/day) and vigorous (minute/day), time in total physical activity (minute/day), total number of sedentary behaviour breaks and average duration of breaks (minute/day), total number of bouts of moderate to vigorous physical activity and average duration of bouts of moderate to vigorous physical activity (minute/day).

### Psychosocial outcomes

As psychosocial parameters, at baseline, at the 12th and after 24 weeks of intervention, the following will be evaluated: perception of health and quality of life, level of anxiety and depressive symptoms and quality of sleep.

The perception of health and quality of life will be evaluated by the EQ-5D-5L instrument, which consists of a page with an objective questionnaire and another page that is a visual analogue scale. The first page consists of five dimensions: mobility, self-care, usual activities, pain/discomfort and anxiety/depression. Each dimension has five levels, ranging from “no problem” to “extreme problem”. The scale is used for the participant to record their general perception of health on a vertical scale, ranging from 0 (“worst health”) to 100 (“best health”).

Anxiety and depression levels will be evaluated by the Hospital Anxiety and Depression (HAD) scale, composed of 14 items, with four possible answers [48, 49]. In addition, the Patient Health Questionnaire (PHQ-9) will be used, an instrument that allows screening for depressive symptoms in adults, consisting of a questionnaire composed of nine questions that assess the presence of symptoms of depression described in the Diagnostic and Statistical Manual of Mental Disorders (DSM-IV). The nine symptoms consist of depressed mood, anhedonia (loss of interest or pleasure in doing things), problems with sleep, tiredness or lack of energy, change in appetite or weight, feelings of guilt or worthlessness, problems concentrating, being slow or restless and suicidal thoughts [50].

Sleep quality will be assessed using the Pittsburgh Sleep Quality Index (PSQI-BR) [51], which consists of a questionnaire consisting of 19 self-administered questions, plus five questions to be answered by the bed partner. The PSQI contains seven domains: subjective sleep quality, sleep latency, sleep duration, habitual sleep efficiency, sleep disturbances, sleep medication use and daytime dysfunction [51].

### Barriers to physical activity

Personal and environmental barriers to physical activity will be obtained using a validated questionnaire for adults [31]. From a list of 19 reasons for not exercising (more), the participant should mark all that apply for them. Personal barriers include the following: “laziness and fatigue (tiredness, physical exhaustion)”, “lack of motivation”, “lack of time”, “lack of partner”, “pain, injury”, “I am not able to”, “I have no way to commute for exercising”, “It is not fun”, “need to relax and rest”, “lack of money”, “lack of competence”, “fear of injuries”, “lack of support”, “I do not understand why it is important” and “body shame”. Environmental barriers include “due to the COVID-19 pandemic”, “lack of appropriate facilities/equipment/space” and “weather”.

### Adverse events and intervening factors

From the medical screening, eligibility criteria, monitoring and safety measures described, and the structure of the rehabilitation programme, we believe that the risk for adverse events, especially serious ones, is minimal. Furthermore, physical tests of greater cardiovascular overload will only be performed in a hospital environment or in the presence of a physician, for greater patient safety. However, if any event occurs, the patients will be treated immediately by the team involved in the research.

During the intervention, patients who are in the intervention group will respond every Friday to a recall questionnaire of adverse events of the last 7 days. Patients will answer simple questions about possible events, unusual physical activity, medication changes, diagnoses and medical care, pain related or not to physical activity, and general well-being. Patients in the control group will be contacted via video call every 6 weeks to control adverse events and will answer the same questionnaire applied weekly to the intervention group.

The possibility of discontinuation of the study will be discussed by the three coordinators ([name], [name] and [name]) in the event of a serious adverse event or a succession of mild and moderate adverse events.

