### Sample size calculation

The sample size calculation was based in an RCT [19] with a population and design similar to the present study. The calculation was performed for the distance covered in the 6-min walk test, the primary exercise outcome of the present study. This aforementioned study showed within-group and between-group changes (i.e. improvement of 50 m on the distance covered) after intervention in favour of the experimental group, which would be expected in the present study. The calculation was performed using the G*POWER 3.1 programme, adopting a significance level of 0.05, a power of 80% and a correlation coefficient of 0.5. The resulting *n* is 22 participants in each group. Considering a likely sample loss of around 30%, the recruitment will aim to reach an *n* sample of 30 participants for each group, totalling around 60 participants. The expected flow of participants into the trial is six to eight participants (blocks) every 15–25 days.

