### Intervention

The intervention will last 24 weeks and will consist of two weekly training sessions in the first 11 weeks, reassessments in the 12th week and three weekly sessions from the 13th to 24th weeks. The planned training will have two major stages, the first consisting of two mesocycles, with progression primarily in volume, and the second consisting of three mesocycles, with progression primarily in the intensity (Table 1).

**Table 1 Tab1:** Structuring of training sessions throughout the Rehabilitation Program (CORE-Study)

**Weeks**	**Structure (Component-type, volume, intensity, progression)**
1	Familiarisation with the training model (focus on learning movements and perceived effort)
2 a 6	**Balance**—3 exercises performed in three sets of 10–30 s, with evolution in time (10 to 30 s) and complexity (stages). Unipedal balance—standing on one foot, balance transitioning from dorsiflexion to plantar flexion, and getting up from a chair and walking in a straight line. The stages are (1) Support from both hands (chair/instructor/wall); (2) One-handed assistance (chair/instructor/wall); (3) No assistance; (4) With eyes closed. **Aerobic (treadmill walking)**—total: 25 min accumulating 15 min of light intensity (RPE: 12/13) and 9–10 min of passive recovery). Duration of blocks in two levels—5 repetitions of 3-min walk with 2-min passive intervals, or 3 repetitions of 5-min walk with 3-min passive intervals. **Resistance (body weight and rubber band)**—Stretch bench press, Sit and Stand, Neutral Rubber Row, Step Up and Down Step and Plantar Flexion (2 sets of 10 to 15 reps at RPE 12/13, interval of 1 min).

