### Randomisation

Patients included in the study will be randomly allocated to one of the two groups. One group will undergo a clinical and functional rehabilitation programme, and the other group will be considered a control, without exercise intervention.

The allocation list will be concealed from all outcome assessors. In order to balance the groups in terms of number of participants, as well as between men and women, a 1:1 block randomisation will be used, stratified by sex. The randomisation process will be carried out using an online software *www.randomizer.org*. This stage will be performed by a researcher who will not be involved in the other experimental procedures of the study.

After baseline evaluations of each patient block, one manager of the study will send the code identifiers of the patients for randomisation by e-mail. This same manager receives by e-mail the allocation list and informs the exercise training providers, while the other manager, responsible for the contact with patients, informs the patients individually about allocation and corresponding procedures (starting training or control procedure meeting).

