Based on the aforementioned context, we highlight how relevant it is to measure the long-term impact that physical training can provide to patients in each of the variables that will be analysed. As for the outcomes of our study, we expect that the physical training prescription performed, based on all the previously highlighted criteria, can present promising results even after 24 weeks of physical training supervision, especially regarding our primary outcome (functional capacity according to the 6-min walk test).

We understand that the results of the present study may allow for benefits to be extrapolated which are directly related to the target population of the study; this may have important implications for the optimisation of physical training prescriptions in outpatient rehabilitation programmes.

This clinical trial protocol and its future findings should have important implications. Exercise professionals will be able to use the practical approach adopted for better conduct of its training prescriptions for this population, especially by customisability of protocol. From a theoretical perspective, there is pioneering analysis of the medium (11 weeks) and long-term (24 weeks) effects of the progressive multicomponent training with respect to several important outcomes, using robust methodological control. Clinically, the study will allow a new and safe tool for clinical decision-making, providing data about safety, adherence and the efficacy of multicomponent training in post-COVID-19 scenarios. Finally, the present training protocol, being evidenced as safe and effective, will support the creation of exercise programmes for post-COVID rehabilitation in public health, as well as the performance of other studies with a more pragmatic approach.

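### Adverse events are asked about weekly in the exercise arm but only every 6 weeks in controls, so any between-arm safety comparison would be biased against exercise, by up to about six-fold for counts of short-lived events

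*Protocol article*

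**What the plan says.** The protocol article sets the two schedules in its section *Adverse events and intervening factors*. Exercise-arm patients "will respond every Friday to a recall questionnaire of adverse events of the last 7 days". For the other arm, "Patients in the control group will be contacted via video call every 6 weeks to control adverse events", and they "will answer the same questionnaire applied weekly to the intervention group". The form asks about possible events, unusual activity, medication changes, diagnoses and medical care, pain and well-being. The article gives no separate recall period for controls and describes no other route for collecting their events.

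The *Intervention* section fixes the duration: "The intervention will last 24 weeks". Under *Randomisation*, "a 1:1 block randomisation will be used, stratified by sex", so arm size does not offset the difference in contact.

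Safety is one of the things the trial is meant to deliver. The *Discussion* speaks of "providing data about safety, adherence and the efficacy of multicomponent training in post-COVID-19 scenarios", and the abstract says much the same.

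**The concern.** A control arm helps a safety assessment only if both arms have the same chance of having an event recorded. Here the exercise arm is asked about every week of follow-up, and controls, on the plain reading, about one week in six. Pain, a short illness or a medical visit in the weeks between would be recorded in one arm and could be missed in the other.

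If the true rates were equal, training would appear to cause events. If training did cause some excess, the reader could not tell it from the effect of asking more often. This is a matter of data collection, so an analysis plan could limit the damage but could not recover control weeks that nobody asked about.

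**Working it through.** The plan gives no figure for event ascertainment, so there is none to reproduce. The check applies arithmetic to the stated schedules.

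**Inputs from the article.** Follow-up 24 weeks; exercise arm weekly with 7-day recall; controls every 6 weeks with the same form; 1:1 allocation; target of 30 per arm ("the recruitment will aim to reach an *n* sample of 30 participants for each group").

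**Observed time.** Windows = weeks ÷ contact interval; days = windows × 7.

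- Exercise: 24 ÷ 1 = 24 windows; 24 × 7 = 168 days.
- Control: 24 ÷ 6 = 4 windows; 4 × 7 = 28 days, and 28 ÷ 168 = 16.7%.
- Ratio: 168 ÷ 28 = 6.0.

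If the exercise arm skips the Friday of reassessment week 12, the ratio is 23 ÷ 4 = 5.75. With 3 or 5 control calls instead of 4, it is 24 ÷ 3 = 8.0 or 24 ÷ 5 = 4.8.

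**If controls are asked about a longer period.** With four calls, weeks covered = 4 × recall weeks. Recall of 2, 3 or 6 weeks covers 8, 12 or 24 weeks, giving ratios of 24 ÷ 8 = 3, 24 ÷ 12 = 2 and 24 ÷ 24 = 1.

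**If events last.** Suppose an event starts at a random time and is still present d weeks later. A 7-day window every 6 weeks then catches it with probability min(1, (1 + d) ÷ 6), while weekly forms catch it always. For d = 0, 1, 2 and 5 weeks the ratio is 6, 3, 2 and 1.

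**Proportion of patients with at least one recorded event.** The article gives no event rate, so a range is assumed, equal in both arms. With Poisson events at rate r per week, the proportion is 1 − exp(−r × weeks covered), with 24 weeks covered against 4.

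| Assumed r per week | Expected count per patient, exercise v control | Proportion with ≥ 1, exercise v control | Ratio of proportions |
|---|---|---|---|
| 0.01 | 0.24 v 0.04 | 21.3% v 3.9% | 5.4 |
| 0.05 | 1.2 v 0.2 | 69.9% v 18.1% | 3.9 |
| 0.10 | 2.4 v 0.4 | 90.9% v 33.0% | 2.8 |
| 0.20 | 4.8 v 0.8 | 99.2% v 55.1% | 1.8 |

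The count ratio stays at 6 throughout, while the ratio of proportions falls as events become common.

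**Chance of a spurious finding, if someone tested it.** With 30 per arm and a two-sided 5% test of two proportions, power = Φ[(|p₁ − p₂| − 1.96 × SE₀) ÷ SE₁], where SE₀ is the pooled and SE₁ the unpooled standard error. At r = 0.05: (0.518 − 1.96 × 0.128) ÷ 0.109 ≈ 2.4, so about 99%. At r = 0.01 it is about 53%, a rougher figure because the counts are small. The true rates are equal in both cases.

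**The case against.** The strongest reply is that the article plans no between-arm safety comparison. Adverse events are neither the primary outcome nor among the listed secondary outcomes, and the *Analysis plan* section names no test for them. The promised safety data could be a description of the exercise arm alone, and closer watch on patients in training has a rationale of its own. This stands in part: the harm is conditional on someone comparing the arms. But controls are asked the same questions, and a controlled trial that reports on safety invites that comparison.

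The second reply is that the 7-day window is attached only to the exercise-arm sentence. The control form might cover the whole interval since the last call. That is possible, and it is why six-fold cannot be stated as fact. Keeping the form's 7-day window is still the plainer reading, and nothing in the article sets a longer one. If 6 weeks was meant, patients in one arm would remember over a week and in the other over six, so recall would still be unequal, by an amount the document gives no means to size.

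The third reply is that the bias runs against the intervention and leaves the walk-test outcome alone. Both are true, and they lower the priority.

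A reader might infer that the safety results are certain to be wrong by a factor of six, whatever the measure. The article does not support that. The factor depends on an unstated recall period and on the number of calls, it applies to observed time and to counts of short-lived events, and no formal comparison is specified. Nor do the schedules point to a falsely reassuring result, since the distortion is towards more recorded events under training.

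**Conclusion.** The point holds in a limited form. As written, the plan gives the arms unequal ascertainment of adverse events, and no other section evens it out. On the plain reading, with four calls, controls are asked about roughly 28 of 168 days, so equal true rates could give up to about six times as many recorded short-lived events under training. The figure is lower for patient-level proportions and lasting events, and under a longer control recall. It would be 8.0 if only three calls were made. Serious events that surface by other routes would also be less affected.

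Any between-arm comparison that ignores this would be biased against exercise, and a true excess could not be told apart from the artefact. This should be fixed, but it does not threaten the primary analysis.

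**What to change.** 1. **Follow-up still running.** Use the same questionnaire, frequency and recall period in both arms, for example a weekly electronic form for controls. *Trial status* puts the last block's recruitment in October 2022, with 24 weeks of follow-up, and dates the protocol version 1 December 2022. Some follow-up was therefore open at that date, though much had passed.
2. **State the recall period used so far for controls.** The size of the problem and the right correction both depend on it.
3. **Data already collected.** Limit the between-arm comparison to exercise-arm windows that match the actual control call dates and recall period, as rates per observed person-week. Do not assume calls at weeks 6, 12, 18 and 24, because the article gives no dates. Report the other exercise-arm events descriptively, without comparison.

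**Cost.** There is a small extra burden for about 30 controls, and someone must review the replies. The matched comparison uses fewer exercise-arm events: with four 7-day windows and complete replies, 30 × 4 = 120 of 30 × 24 = 720 exercise person-weeks. A change in mid-course also leaves earlier and later control follow-up collected differently, which the report should say.

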### Sanitary measures

All assessments and physical training sessions will respect the recommended health measures to prevent the spread of COVID-19. Especially in relation to the intervention, it is important to note that the exercise sessions will be held in a ventilated environment and all participants (patients and staff) will be required to wear masks.

Disposable masks will be made available to participants so that they can change them whenever they are wet, and a distance of 1.5 m will be respected between participants and members of the research team. The training providers involved in the project will use PFF2 masks. In addition, all participants must wash their hands before the start of training and will have free access to hand sanitiser throughout all sections. There will be a break (between 20 and 30 min) between classes for complete cleaning of the training place and the equipment involved in the practices.

### Ethical considerations

This project has been approved by the Ethics Committee in Research with Human Beings of the Federal University of Santa Catarina, under protocol number 49487721.9.0000.0121. All participants will be duly informed about all study procedures and, after agreeing to participate, participants will sign the free and informed consent form. In the consent form, the risks and benefits of the study are well delineated. In summary, patients will be informed that participation in the study involves a minimal probability of risks and discomforts, especially by the professional prescription and conduction of the exercise sessions. The research team, consisting of physicians, exercise professionals and other health professionals, will be available for solving any adverse events. Sanitary measures are also made clear. The common discomforts during and after the exercise sessions, such as fatigue, are also explained to patients, which may require reducing the intensity or stopping the exercise.

Any important modification to the protocol that is needed will be discussed among coordinators and managers in monthly meetings and reported to the evaluation team, the ethics committee and the trial registry (ReBEC).

### Coordination and management of the trial

[name], [name] and [name] comprise the trial’s coordinating team. While [name] coordinates the clinical triage of patients, [name] and [name] coordinate the outcome assessment team, the team responsible for patient allocation and the intervention team. The coordinating centre is located in the rehabilitation centre of the sports centre (CDS) of UFSC. There is no specific steering committee or endpoint adjudication committee for this trial. The roles and responsibilities from these committees also belong to the coordination centre. The trial has three managers, [name], [name] and [name], who will carry out part of the recruitment, perform the scheduling and logistical organisation of the evaluations.

### Data management

The outcome assessors will perform a first treatment of the data when necessary, save a file and send the data to the trial managers. Meetings between the study management and the evaluators will be held to define the form and dates for sending the data. With the data in hand, all will be tabulated in a standardised way in a central folder of the trial, which will be evaluated and organised by the coordinators and managers.

### Data monitoring

There is no specific monitoring committee for this trial. All data are monitored by specific evaluation teams for each outcome group (i.e. cardiovascular outcomes team, functional outcomes team) and sent to trial managers, who check and organise the central database. It is important that this trial is unfunded, and all researchers have no conflicts of interest.

### Analysis plan

Continuous sample characterisation variables will have their normality and homogeneity tested by the Shapiro-Wilk and Levene tests, respectively. Those with normal distribution will be described by mean and standard deviation, and the others will be described by median and interquartile range. The categorical variables of sample characterisation will be described by absolute frequency (*n* sample) and relative (%).

To analyse the effects of the rehabilitation programme, generalised estimation equations will be used, adopting the Bonferroni post hoc. Outcomes will be analysed in two ways (by protocol [PP] and intention to treat [ITT]). For this, patients who complete at least 70% of the proposed sessions will be included in the PP analysis. For ITT analysis, all available data of all patients will be used. For this, all patients will be invited for endpoint evaluations, independently of adherence. For missing data, multiple imputation considering the maximum likelihood estimation approach will be used. Effect sizes (ES) will be calculated using Cohen’s *d* test (Cohen 1988), being considered as small values (0.20 ≤ *d* < 0.50), medium (0.50 ≤ *d* < 0.80) and great (*d* ≥ 0.80).

The significance index adopted will be 0.05. The statistical treatment of the data will be carried out using SPSS (Statistical Package for the Social Sciences), version 22.0.

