### Primary outcomes

The primary outcome was the functional indicator of cardiorespiratory fitness after 24 weeks assessed by the 6-min walking test (6MWT), following the protocol of the American Thoracic Society [21] and recorded as 6MWD in meters.

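### The plan sizes 6MWD at an unadjusted 0.05 but does not exempt the week-24 arm difference from the Bonferroni post hoc, so the primary test may have less than the planned 80% power

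*Protocol article*

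**What the plan says.** - **Sample size calculation.** The calculation is for 6MWD, "adopting a significance level of 0.05, a power of 80% and a correlation coefficient of 0.5". It cites an earlier trial with within-group and between-group changes and expects an "improvement of 50 m on the distance covered". The result "is 22 participants in each group", raised to 30 per group for a loss of around 30%. No multiplicity adjustment, SD or G*Power test family is given.
- **Primary outcomes.** "The primary outcome was the functional indicator of cardiorespiratory fitness after 24 weeks", measured by the 6-minute walk test.
- **Functional capacity.** 6MWD is measured at baseline, at week 12 and after 24 weeks.
- **Analysis plan.** To estimate programme effects, "generalised estimation equations will be used, adopting the Bonferroni post hoc", with a significance level of 0.05. The same sentence serves every outcome. It does not treat 6MWD separately, name a contrast that decides the trial, or say which comparisons the Bonferroni correction covers.

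**The concern.** The sample size rests on an unadjusted 0.05, and the primary outcome is tied to one visit. The only route the Analysis plan gives to an arm comparison at a particular visit is the Bonferroni post hoc step. If the week-24 difference is corrected together with other pairs, the test is run at a smaller level than the one used for sizing. Those other pairs could include the arm difference at baseline, where randomisation already makes the null hypothesis true. Power for the planned 50 m effect would then be spent on comparisons the primary question does not need.

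This goes beyond detail that an article may leave to a fuller document. The article does state a method, and that method fits the trial's own primary question less well than a single week-24 contrast would.

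**Working it through.** **Inputs from the article.** Significance level 0.05, power 80%, correlation 0.5, effect 50 m, 22 evaluable per group, target 30 per group, loss about 30%, two arms, three visits for 6MWD.

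**Assumptions.** Two-sided test; two-sample t-test; SD back-solved because none is given.

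**1. The plan's own figure.** Without an SD, 22 per group cannot be reproduced. It can be inverted. Power of the t-test uses the noncentral t with df = 2n − 2 and noncentrality d × √(n/2). Setting n = 22, level 0.05 and power 0.80 gives d = 0.865, hence SD = 50 / 0.865 = 57.8 m. The noncentrality is 0.865 × √11 = 2.87.

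The correlation of 0.5 does not disturb this. The SD of a change score is SD × √(2(1 − 0.5)) = SD, so a t-test on change has the same d. A repeated-measures interaction with two measurements and 44 in total needs f = 0.216, and 4 × 0.216 = 0.865, the same effect. With three measurements it needs f = 0.194, and the figures below would shift.

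**2. Possible Bonferroni families.** Two arms by three visits give 6 cells and 6 × 5 / 2 = 15 pairs: 3 between arms at the same visit, 6 within an arm and 6 mixed. Plausible values of k are:
- k = 1: arms compared within each visit, each visit its own family.
- k = 2: arm differences at weeks 12 and 24.
- k = 3: arm differences at all three visits.
- k = 9: those 3 plus the 6 within-arm pairs.
- k = 15: all pairs.

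**3. Power for the week-24 difference at level 0.05/k, d = 0.865.**

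| k | Level | 21 per arm | 22 per arm | 30 per arm | n per arm for 80% |
|---|---|---|---|---|---|
| 1 | 0.05 | 78.1% | 80.0% | 90.9% | 22 |
| 2 | 0.025 | 68.2% | 70.5% | 85.0% | 27 |
| 3 | 0.0167 | 62.1% | 64.6% | 80.8% | 30 |
| 9 | 0.0056 | 45.8% | 48.6% | 67.9% | 37 |
| 15 | 0.0033 | 38.8% | 41.5% | 61.4% | 41 |

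The 21 is 30 × (1 − 0.30); the 30 is full retention. The largest loss at 22 per arm is 80.0 − 41.5 = 38.5 points.

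**4. If the group-by-time effect is the primary test.** It has (2 − 1) × (3 − 1) = 2 degrees of freedom. Assume compound symmetry with correlation 0.5. With the effect in SD units, the two changes from baseline have variance 1 and covariance 0.5. For arm differences c₁ (week 12) and c₂ (week 24), the noncentrality is (n/2) × (4/3) × (c₁² + c₂² − c₁c₂).
- Linear build-up, c₁ = d/2 and c₂ = d: 11 × d² = 11 × 0.748 = 8.22. Wald chi-square power is 73% (71% with an F reference).
- Full effect by week 12, c₁ = c₂ = d: 11 × (4/3) × 0.748 = 10.97. Power is 85% (84% with F).

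**5. One baseline-adjusted week-24 contrast at 0.05.** Adjustment at correlation 0.5 multiplies the residual SD by √(1 − 0.5²) = 0.866, so d becomes 0.865 / 0.866 = 0.998. With 22 per arm, power is about 90%; with 21 it is about 88%.

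**The case against.** The article never says that a post hoc pair decides the primary hypothesis. Post hoc comparisons ordinarily follow a model test, so the primary test may be the group-by-time effect at 0.05, which would match the level used for sizing. If the correction is applied to the two arms within each visit, there is one pair per visit and no penalty. A correlation among the sample size inputs points to a repeated-measures calculation, so the t-test behind the power figures is itself an assumption. All patients are to be invited to the final evaluation whatever their adherence, and with all 30 per arm retained power is still 80.8% at k = 3. Finally, a Bonferroni correction is conservative and does not inflate false positives.

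All of this stands, and it makes the loss conditional. It does not remove the point. The article does not exempt the week-24 difference. The interaction test, if that is what is meant, can be significant because of week 12 alone and does not answer the week-24 question. Full retention is also not what the article expects: "Considering a likely sample loss of around 30" per cent is its own phrase.

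A reader might infer that within-arm improvement will be counted as success, since the sample size paragraph mentions within-group changes. The documents do not support that. The design is a parallel superiority trial against control, and no sentence makes within-arm change a criterion.

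**Conclusion.** The point holds in conditional form. The sample size uses an unadjusted 0.05 and the primary outcome is fixed at week 24, but the stated analysis neither names that contrast nor protects it from the correction. At 22 per arm the cost runs from nothing (k = 1) through about 10 points (k = 2) and 15 points (k = 3) to about 39 points (k = 15). Under the group-by-time reading, power is about 73% to 85%, depending on when the effect appears.

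These figures rest on a two-sided t-test, an SD of about 57.8 m inferred from n = 22, and, for the interaction, compound symmetry with correlation 0.5.

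A reader might infer that the primary comparison is definitely run as a corrected pair, that 80% power is therefore not delivered, or that the week-24 pair is the only comparison the trial was sized for. The article supports none of these: the family size, the SD and the sizing test are all unstated, and the sample size section names 6MWD but not the week-24 pair.

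**What to change.** In the Analysis plan, state that the primary analysis is the baseline-adjusted difference between arms in 6MWD at week 24, by one two-sided test at 0.05 without Bonferroni correction, reported in metres with a 95% confidence interval. Keep Bonferroni for the remaining pairs, and say that week 12 and within-arm changes are supportive only.

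The change is to wording alone and needs no patients or data. The Trial status section says the last block was recruited in October 2022, so the analysis wording is the practical lever; it should be settled before outcome data are analysed. The downside is that the other pairwise comparisons lose confirmatory status.
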